### Analytical approach

#### Objective 1: Describing UK treatment patterns for second-line T2DM treatment, and summarising the results of relevant published RCTs to contextualise the study findings

We will describe trends in prescribing for T2DM second-line treatment for the duration of the study period across the UK and between CCGs. This analysis will update previous research which described the same second-line treatment use in the UK from 2000 to 2017, and will employ similar methods.^4^ These descriptive statistics will inform the assessment of the validity of the assumptions that underlie the overall study design. Baseline characteristics listed in the covariates section will also be described for this cohort, overall and stratified by exposure group. We will also conduct a literature review to summarise published RCTs which describe the relative effectiveness of alternative second-line antidiabetic treatments of interest to this study. This will help contextualise the results of this observational study (cf. objectives 2 and 3). We will consider reasons for any possible differences between this observational study compared with published RCTs, including residual confounding and differences in the study populations.

#### Objectives 2 and 3: Instrumental variable (IV) design to estimate relative treatment effectiveness overall and by subgroup

Studies which apply traditional risk adjustment approaches with little information on case severity may provide biased estimates of treatment effectiveness. We will therefore use an IV design^31 32^ to estimate treatment effectiveness in the presence of residual confounding. The IV for second-line drug treatment in this study will be each CCG’s prescribing history, recognising that the choice of second-line treatment may involve the hospital diabetologist, the GP, other healthcare professionals, and the individual. We will define ‘CCG prescribing history’ as the proportion of people prescribed each second-line treatment in the CCG for the last complete calendar year prior to the treatment intensification currently under consideration. This IV encourages receipt of the treatment but does not have a direct effect on outcomes except through the treatment prescribed (figure 2). Using CCG prescribing history as the IV follows pharmacoepidemiological research^32^ that uses provider preference as an instrument for treatment prescribed.

**Figure 2 F2:**
[figure not shown]
Instrumental variable design to be applied in this study comparing three options for second-line antidiabetic treatment. CCG, Clinical Commissioning Group; DPP4i, dipeptidyl peptidase-4 inhibitors; HbA1c, haemoglobin A1c; SGLT2i, sodium-glucose cotransporter-2 inhibitor; SU, sulfonylureas.

In our pilot CPRD data,^4^ the proportions of people prescribed each second-line treatment regimen varied widely. For example, in 2014 the ranges across CCGs were 5%–100% (SU), 0%–90% (DPP4i) and 0%–35% (SGLT2i).^4^ These proportions have changed over time but similar people received different second-line treatment regimens simply according to CCG prescribing preference or time period.^4^

This study’s design will exploit this wide variation in the choice of second-line treatment. We will use this IV to estimate the relative effectiveness of alternative second-line treatments while minimising bias from unobserved confounding. We will use a ‘local IV estimator’^33^ to allow for heterogeneity according to unobserved characteristics (eg, lifestyle choices) as well as observed characteristics (eg, baseline HbA1c) when reporting the relative effectiveness of the alternative second-line treatments according to individual risk factor profiles.

### IV assumptions

The validity of our IV design relies on three key assumptions: the IV must (1) strongly predict the treatment prescribed; (2) be independent of baseline unmeasured covariates; and (3) only affect the outcome through the treatment prescribed.^31^ The IV design will lead to bias if the prescribing history of the CCG has a direct effect on the outcome. We carefully assessed whether the CCG’s prescribing history met the criteria for an IV. Our pilot data showed it was strongly associated with the second-line treatment regimen prescribed (assumption 1). We also found that prescribing history balanced the observed covariates (assumption 2, figure 3). We are unable to assess empirically whether clinicians’ prescribing history is independent of unmeasured confounders; however, it is likely that participants will attend their local GP without considering their prescribing history, and unlikely that the CCGs prescribing history would have a direct effect on outcomes (assumption 3). For example, it is unlikely that simply because a CCG shows a preference for prescribing SU the participants’ outcomes would be better (or worse) regardless of the treatment actually prescribed. We will reassess each assumption using the full study dataset and undertake sensitivity analyses to test these assumptions.

**Figure 3 F3:**
[figure not shown]
Covariate balance across levels of CCG prescribing history (this study’s IV) (2014–2017). BMI, body mass index; BP, blood pressure; CCG, Clinical Commissioning Group; CVD, cardiovascular disease; DPP4i, dipeptidyl peptidase-4 inhibitors; eGFR, estimated glomerular filtration rate; HbA1c, haemoglobin A1c; IV, instrumental variable; SGLT2i, sodium-glucose cotransporter-2 inhibitor; SU, sulfonylureas.

### Power considerations

Power calculations were conducted prior to accessing study data. Clinically meaningful between-treatment difference in HbA1c from baseline is considered to be 0.3 percentage points (eg, from 8.0% to 7.7%) by the European Medicines Agency^34^ and 0.5 percentage points by NICE.^35^ We based our power calculations on these numbers and assuming an SD of 2.4.^36^ We follow methodological recommendations for power calculations with IV designs and consider that the proportion of people who actually receive the treatment predicted by the IV is 80%, but also consider scenarios where the IV is weaker (70% compliance) and stronger (90% compliance).^31^ We require 80% power at the 5% (two-sided) level of statistical significance, with a Bonferroni correction to account for multiple comparisons to get a familywise error rate of 5%. Table 1 shows the requisite sample sizes of the two treatment groups projected to have the fewest participants (SU and SGLT2i). The study will include approximately 25 700 participants (SU=6000, DPP4i=13 000, SGLT2i=6700) based on an initial feasibility count, which will be more than sufficient for detecting whether clinically significant differences in the primary endpoint are statistically significant.

**Table 1 T1:** Required sample size (N) for the IV design according to instrument strength (level of compliance) and magnitude of effect size at 80% power and 5% (two-sided) level of statistical significance

	Level of compliance (IV strength)					
	70%		80%		90%	
Effect size: between-treatment difference in mean HbA1c reduction baseline to 12 months	SU	SGLT2i	SU	SGLT2i	SU	SGLT2i
0.3	4556	1952	3488	1495	2756	1181
0.4	2563	1098	1962	841	1550	664
0.5	1640	703	1256	538	992	425

DPP4i, dipeptidyl peptidase-4 inhibitors; IV, instrumental variable; SGLT2i, sodium-glucose cotransporter-2 inhibitor; SU, sulfonylureas.

### Planned analyses

We will examine the relevant trends in prescribing between 2014 and 2020 by CCG, and by year, and summarise baseline covariates using data collected prior to the index date for second-line treatment.

We will provide personalised estimates of treatment effectiveness using the local IV (LIV) approach^33 37^ to predict the counterfactual outcomes that each person would experience if they were prescribed each second-line treatment. We will use probit regression models^38^ to estimate the propensity to receive each treatment according to observed characteristics, and CCG preference for each second-line regimen (the IV). We will estimate the relationship of each outcome with observed characteristics, and the propensity for each second-line treatment using generalised linear models (GLMs)^39^ for continuous and count outcomes. For time-to-event outcomes (eg, time to second-line treatment cessation, time to each microvascular or macrovascular complication), we will recognise that the period of observation may differ across individuals due to censoring. We will describe each endpoint by plotting Kaplan-Meier curves, and estimate each treatment effect using discrete-time hazard models.^40^ SEs will be calculated with non-parametric bootstrapping, and will account for clustering of individuals within practices.

These models will be used to estimate the relative effect of prescription of SGLT2i vs SU, DPP4i versus SU and SGLT2i vs DPP4i for the primary and secondary outcomes. Person-level treatment effects will be calculated as the difference in predicted outcomes following prescription of the alternative drugs. These person-level treatment effects will be aggregated to report the relative effectiveness of the treatments prescribed overall, and by prespecified subgroups. These prespecified subgroups will include: people with and without CV comorbidities overall and by subtype of CVD, people with baseline eGFR ≥60 mL/min/1.73 m^2^ vs baseline eGFR <60 mL/min/1.73 m^2^, age groups, sex, ethnicity, BMI (based on WHO categorical definition^41^), adherence to metformin and baseline HbA1c levels. We will consider finer eGFR subgroupings, age categories and HbA1c levels based on descriptive statistics (objective 1) prior to any relative effectiveness analyses (objectives 2–3). Any additional subgroups will be informed by descriptive statistics of each covariate, and the advice of a panel of healthcare professionals, building on those identified in a literature review. The clinical panellists will include diabetologists, GPs and practice nurses involved in care for people with T2DM.

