## Introduction

Around 3.5 million people in the UK have been diagnosed with type 2 diabetes mellitus (T2DM) accounting for ~10% of National Health Service (NHS) expenditure.^1^ This proportion is predicted to rise to ~17% by 2035–2036.^2^ T2DM is a progressive disease which requires careful management of blood glucose and diabetes-associated complications.^1^ The National Institute for Health and Care Excellence (NICE) recommends metformin as the first-line antidiabetic treatment in people with T2DM.^1^ In many cases, people with T2DM need further treatment in addition to metformin monotherapy to maintain sufficient glycaemic control.

NICE guidance recommends several drug classes as add-ons to metformin for first-stage intensification, hereafter referred to as second-line treatment. These include sulfonylureas (SU), pioglitazone, dipeptidyl peptidase-4 inhibitors (DPP4i) or sodium-glucose co-transporter-2 inhibitors (SGLT2i).^1 3^ NICE guidance recommends considering individual clinical circumstances when selecting T2DM drug treatment. For instance, SGLT2i are recommended as second-line treatment if the person is at high risk of hypoglycaemia or when SU are not tolerated or are contraindicated.^1 3^ However, these guidelines do not specify a single preferred drug class, either overall or within specific groups sharing clinical characteristics.^1^ Research using a representative sample of the UK primary care population up to 2017 showed that SU, DPP4i and SGLT2i, each in combination with metformin, are the most commonly prescribed second-line treatments.^4^

There is wide variation in the proportion of people prescribed these drugs in addition to metformin across NHS Clinical Commissioning Groups (CCGs), who commission local NHS services, suggesting clinician preference may influence treatment choice.^4^ In particular, the variation in SGLT2i prescribing suggests that some clinicians may prescribe these drugs even for those patients who are not considered at high risk of hypoglycaemia and therefore eligible for SU.

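### Bootstrap SEs cluster on practice while the instrument is shared by whole CCGs, so they are too small if outcomes correlate between practices within a CCG

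*Protocol article*

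**What the plan says.** **Level of the instrument.** The section on the instrumental variable (IV) design for objectives 2 and 3 states: "The IV for second-line drug treatment in this study will be each CCG’s prescribing history". It measures this as "the proportion of people prescribed each second-line treatment in the CCG for the last complete calendar year prior to the treatment intensification". Every person and every practice in a CCG therefore carries the same value in a given year. Planned analyses enters this CCG preference in the probit models for treatment propensity.

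**Level of the standard errors.** The same section says: "SEs will be calculated with non-parametric bootstrapping, and will account for clustering of individuals within practices". The article mentions no resampling of CCGs, no CCG random effect and no other CCG-level variance term. The Sensitivity analyses section names no alternative clustering level.

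**Error rate.** Power considerations says: "We require 80% power at the 5% (two-sided) level of statistical significance, with a Bonferroni correction to account for multiple comparisons". Planned analyses lists three pairwise contrasts, "SGLT2i vs SU, DPP4i versus SU and SGLT2i vs DPP4i for the primary and secondary outcomes", so each is tested at 0.05/3.

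**The concern.** When the variable that identifies an effect is constant within a group, residual correlation of outcomes within that group enters the variance of the estimate. Here that group is the CCG (within a year). A bootstrap that resamples practices treats two practices in one CCG as independent and loses the covariance between them.

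The article gives a reason why such covariance could exist, since it describes "NHS Clinical Commissioning Groups (CCGs), who commission local NHS services". It does not report the covariance.

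At stake is the width of the intervals for the primary HbA1c contrasts, and for any other IV estimate with residual CCG correlation. Bonferroni control at 5% works only if each single test holds its own level.

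**Working it through.** **1. The plan's own figure.** Table 1 gives 3488 (SU) and 1495 (SGLT2i) for effect 0.3 at 80% compliance. Inputs: SD 2.4, power 80%, alpha 0.05/3 two-sided (z = 2.394 and 0.842), and a 70:30 split inferred from the table.

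n(SU) = (2.394 + 0.842)² × 2.4² × (1 + 7/3) / (0.3 × 0.8)² ≈ 3490, and n(SGLT2i) = 3/7 of that ≈ 1496.

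All 18 cells agree within 2 patients. No clustering term is needed, so nothing in the sample size compensates for CCG correlation.

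**2. Design effects.** N = 25 700 is from the article. The counts and ICCs are assumptions: 150 CCGs (171.3 people each), 1500 practices (17.13 people each), practice ICC 0.02.

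- True: D = 1 + (17.13 − 1) × 0.02 + (171.3 − 1) × ICC_CCG
- Seen by practice clustering: P = 1 + (17.13 − 1) × (0.02 + ICC_CCG)
- SE ratio R = √(D/P)
- Actual error = 2 × [1 − Φ(z/R)], with z = 1.96 at 5% and 2.394 at 0.05/3

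| CCG ICC | D | P | R | Error at 5% | Error at 1.67% |
|---|---|---|---|---|---|
| 0 | 1.32 | 1.32 | 1.00 | 5.0% | 1.7% |
| 0.002 | 1.66 | 1.35 | 1.11 | 7.7% | 3.1% |
| 0.005 | 2.17 | 1.40 | 1.24 | 11.5% | 5.4% |
| 0.01 | 3.03 | 1.48 | 1.43 | 17.0% | 9.4% |
| 0.02 | 4.73 | 1.65 | 1.70 | 24.8% | 15.8% |

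At CCG ICC 0.005 the Bonferroni bound for three contrasts is 3 × 5.4% = 16%, not 5%. This is an upper bound. The actual familywise rate was not computed.

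**3. Simulation under no effect.** Linear two-stage least squares (2SLS), one contrast, N = 25 700, an unmeasured confounder, year adjustment, practice ICC 0.02 and 1000 replicates per cell. The instrument was either fixed over years or had 70% of its variance persistent. SEs were analytic cluster-robust. A true 5% rate has a Monte Carlo SE of √(0.05 × 0.95/1000) = 0.7 points.

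Rejection at nominal 5%, practice-clustered / CCG-clustered:

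| CCG ICC | 100 CCGs × 12 practices, fixed | 100 × 12, 70% | 190 × 7, fixed | 190 × 7, 70% |
|---|---|---|---|---|
| 0 | 5.3 / 5.7% | 5.6 / 5.6% | 6.4 / 6.9% | 4.3 / 4.4% |
| 0.002 | 7.9 / 5.3% | 7.9 / 5.0% | 6.4 / 3.9% | 5.8 / 4.5% |
| 0.005 | 12.0 / 5.0% | 13.7 / 6.4% | 10.0 / 5.5% | 8.3 / 5.3% |
| 0.01 | 21.5 / 6.5% | 18.2 / 5.3% | 14.2 / 6.2% | 11.9 / 4.8% |
| 0.02 | 32.4 / 7.0% | 30.1 / 5.6% | 19.1 / 4.9% | 18.0 / 5.4% |

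Example (100 CCGs, fixed instrument, CCG ICC 0.01): the true SD of the estimate is 0.170, the mean practice-clustered SE 0.106 and the mean CCG-clustered SE 0.162.

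Further runs of the same kind, with up to 200 CCGs, stretch the ranges slightly, to 6-10% at CCG ICC 0.002 and to 4-8% for CCG clustering.

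**The case against.** **The size is unknown and may be nil.** What matters is the correlation left after adjustment for baseline HbA1c, deprivation, age, practice size, comorbidities and the rest. The article does not report it. This stands: a reader might infer that every interval in objectives 2 and 3 is too narrow, but nothing in the article establishes that. At CCG ICC 0 the practice bootstrap is adequate.

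**Identification is not only between CCGs.** The instrument is updated each year, and the IV design section says that prescribing proportions changed over time. This also stands, so it would be too strong to say that all information comes from contrasts between CCGs. In the runs above, yearly change mostly softened the inflation but did not remove it. The 70% persistence is itself an assumption.

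**The simulation is a stand-in.** The plan uses a probit and GLM local IV estimator with three treatments, and discrete-time hazard models for time-to-event outcomes. None of these was simulated, so the percentages should not be carried over to objective 3.

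**A valid instrument is independent of CCG factors.** That protects against bias. CCG-level variation unrelated to the instrument leaves the estimate unbiased but still adds to its variance, so this does not answer the point.

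**It is a detail for the analysis plan, or is covered by the robustness checks.** The article states the practice level outright, so this is a fixed choice and not an omission. The sensitivity analyses promise alternative statistical models but do not mention the clustering level.

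**Conclusion.** The mismatch holds as stated: the instrument is set by CCG and year, and the SEs are clustered by practice. Its consequence is conditional. Under positive residual CCG correlation the SEs are too small and the 5% familywise rate is not assured; under zero correlation there is no inflation.

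Under the assumptions above (100-200 CCGs, practice ICC 0.02, linear single contrast), practice-clustered type I error at nominal 5% is about 5%, 6-10%, 8-14%, 12-22% and 18-32% at CCG ICC 0, 0.002, 0.005, 0.01 and 0.02. The top of that range needs a CCG ICC as large as the assumed practice ICC, and nothing in the article supports that. Point estimates are unaffected.

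**What to change.** Replace the SE sentence in Planned analyses with: *SEs will be obtained by a non-parametric cluster bootstrap that resamples whole CCGs, keeping all practices and years of a CCG together because CCG effects persist over time, and re-estimates both stages in each replicate; practice-level clustering will be reported as a sensitivity analysis.*

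Persistence is the reason to resample CCGs and not CCG-years. Practices nest within CCGs, so clustering within practices is still respected.

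The cost is a change of wording and of the resampling unit in the code. Intervals will be wider where CCG correlation is present. With fewer and larger resampling units, bootstrap replicates will be less stable for rare outcomes and small subgroups. CCG clustering is also only approximately exact (about 4-8% in the runs).

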### Missing data

In our primary analysis, we will use a complete-case approach based on the main potential confounders listed in the covariates section. We will conduct secondary analyses using complete cases for the full list of potential confounders, including those expected to have a high proportion of missing data (see covariates section), which we do not expect to be missing at random. Because we cannot assume covariate measurements are missing at random and the IV model is computationally intensive, we will not use multiple imputation.

We will adopt two main approaches based on the type of missingness for outcome data: (1) linear interpolation using values recorded during follow-up, and (2) inverse probability weighting (IPW) to those people lost to follow-up with no subsequent outcome measure. We will use linear interpolation for values that are intermittently missing during follow-up, for example, if HBA1c at 12 months is required, but the available measures are at 3-month and 17-month follow-up, which fall outside the requisite time window (9–15 months). This method was used in precedent diabetes research with observational data.^42^ For those settings, were the patient is lost to follow-up and there is therefore no subsequent HbA1c measure available, we will use IPW, reweighting the data for those with available observations to represent the group lost to follow-up, assuming therefore that the HbA1c data are missing at random.^42 43^

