### Covariates

We will use primary care demographic data, diagnosis codes (Read or SNOMED for CPRD Gold and Aurum, respectively), and laboratory test results recorded prior to second-line treatment initiation, to define our main list of potential confounders. These include age, sex, IMD, time on first-line antidiabetic treatment (as a proxy for diabetes duration), GP size, relevant coprescriptions prescribed within 60 days of second-line treatment initiation (renin-angiotensin system inhibitors, statins), history of proteinuria and comorbidities at baseline (myocardial infarction (MI), unstable angina, stroke, ischaemic heart disease, hypoglycaemia, congestive heart failure (CHF), chronic kidney disease (CKD), end-stage renal disease (ESRD), cancer (any), advanced eye disease and lower extremity amputation). CKD status will be defined using serum creatinine test results to derive eGFR, using cut-points defined by the Kidney Disease Improving Global Outcomes guidelines for CKD, but without requiring two measures 3 months apart.^26^ We will also identify HbA1c, systolic blood pressure (SBP), diastolic blood pressure (DBP), eGFR, body weight and body mass index (BMI)^27^ using values recorded in the 180 days period before the second-line antidiabetic treatment initiation date in the primary care record. Time between baseline clinical measures and second-line treatment initiation will also be included as covariates. We will follow previous observational research,^28^ in undertaking secondary analyses that include additional potential confounders that are defined in primary care records, but for which we anticipate relatively high levels of missing data, namely: ethnicity, high-density lipoprotein (HDL), low-density lipoprotein (LDL), total cholesterol, triglycerides, smoking and alcohol status. In the HES-linked cohort, we will use International Classification of Diseases 10th Revision (ICD-10) diagnosis codes recorded as part of previous hospitalisations in conjunction with primary care data to define comorbidities. We will also use ethnicity recorded in HES for people whose ethnicity is missing within the primary care data. Codelists for all covariates defined in primary and secondary care will be published alongside study results.

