### Sensitivity analyses

We will conduct sensitivity analyses falling under three broad categories: (1) Modified study population inclusion and exclusion criteria to evaluate the validity of our IV assumptions in subgroups where there is arguably less equipoise in the choice of second-line treatment^44^; (2) Comparing the larger primary care unlinked cohort with the primary care population linked to secondary care data (HES) and (3) Evaluating the robustness of our statistical methods.

Under the first category of sensitivity analyses, we will exclude people with contraindications for SU (eg, liver disease) who are prescribed SGLT2i, as this prescribing may not be due to CCG preference. We will also expand the eGFR exclusion to all those with eGFR <60 mL/min/1.73m^2^ (vs eGFR <30 mL/min/1.73m^2^ in the main analysis). In addition, we will include people who are censored or die during the first 60 days after a prescription for SU, DPP4i or SGLT2i without a prescription for metformin in the same time period to consider the impact of potentially misclassifying these people as switching from metformin monotherapy instead of adding on to metformin monotherapy. Under the second category of sensitivity analyses, we will repeat the analyses for objectives 1 and 2 limited to the HES-linked subpopulation from CPRD who are eligible for the long-term outcomes (objective 3). Third, we will assess the robustness of findings to alternative statistical models for the LIV approach, outcome regressions and alternative approaches to handling missing data.^45^

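### The extended-confounder analysis changes the adjustment set and the analysed sample together, so its difference from the primary result cannot be attributed to the added confounders

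*Protocol article*

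**What the plan says.** All references are to the Protocol article.

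- **Primary analysis (Missing data):** "In our primary analysis, we will use a complete-case approach based on the main potential confounders listed in the covariates section".
- **Secondary analysis (Missing data):** "We will conduct secondary analyses using complete cases for the full list of potential confounders".
- **Added variables (Covariates):** these are described as potential confounders "but for which we anticipate relatively high levels of missing data, namely: ethnicity, high-density lipoprotein (HDL), low-density lipoprotein (LDL), total cholesterol, triglycerides", followed by smoking and alcohol status. That makes seven variables.
- **Mechanism (Missing data):** the added variables are ones "which we do not expect to be missing at random". Partly for that reason, and partly because of computing time, "we will not use multiple imputation".
- **Effect heterogeneity (text under Figure 2):** the local IV estimator is chosen "to allow for heterogeneity according to unobserved characteristics (eg, lifestyle choices) as well as observed characteristics (eg, baseline HbA1c".
- **Averaging (Planned analyses):** person-level effects are aggregated over the analysed people to give the overall effect.
- **Sensitivity analyses:** the only related commitment is to assess "alternative approaches to handling missing data", with no model or sample named.

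**The concern.** Between the primary and secondary analyses two things change at once: the variables adjusted for and the people analysed. Nothing in the text separates them. The natural use of an analysis with extra confounders is to set it beside the primary result and ask whether leaving those variables out mattered. As specified, that comparison can mislead in both directions. A shift may appear although the added variables confound nothing, because those with complete records respond differently from those without. Equally, agreement between the two estimates may conceal a confounding effect offset by a selection effect. At stake is what the secondary analysis can show about smoking, alcohol, ethnicity and lipids.

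**Working it through.** **1. The plan's own precision figures.** Power considerations gives SD 2.4, 80% compliance as the base case, 80% power and a two-sided 5% level with Bonferroni correction. Taking three comparisons (α = 0.05/3) and the 7:3 SU:SGLT2i allocation implied by Table 1:

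n(SU) = (2.394 + 0.842)² × 2.4² × (1 + 7/3) / (0.3 × 0.8)² ≈ 3490, and n(SGLT2i) = 3/7 × 3490 ≈ 1496.

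Table 1 states 3488 and 1495. All nine rows reproduce within 2 patients, so dividing by compliance is the plan's own precision model and is used below.

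**2. Standard error before restriction.** With the feasibility counts (6000 SU, 6700 SGLT2i):

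SE = 2.4 × √(1/6000 + 1/6700) / 0.8 = 0.053 HbA1c points.

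**3. Retention.** The protocol gives no recording rates. Assume each variable is 80% to 95% recorded.

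- All seven missing independently: 0.80⁷ = 21% to 0.95⁷ = 70% retained.
- Four lipids missing as one block, so four independent units: 0.80⁴ = 41% to 0.95⁴ = 81% retained.

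**4. Chance difference between the two estimates.** Suppose the smaller sample is a random subset and the added covariates do nothing. With r the fraction retained, SE(difference) = SE × √(1/r − 1).

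| Assumption | r | SE in subset | SE of difference | 95% range | Share of 0.3 |
|---|---|---|---|---|---|
| Lipids as block, 95% | 0.81 | 0.059 | 0.025 | ±0.05 | 17% |
| Lipids as block, 80% | 0.41 | 0.083 | 0.064 | ±0.13 | 42% |
| All independent, 95% | 0.70 | 0.064 | 0.035 | ±0.07 | 23% |
| All independent, 80% | 0.21 | 0.116 | 0.104 | ±0.20 | 68% |

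The 0.3 is the smaller of the two clinically meaningful differences in Power considerations. These ranges are sampling noise only and contain no selection effect.

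**5. Selection without confounding.** This is an illustration with assumed inputs, using a two-stage least squares IV model rather than the local IV estimator. Half the people have an effect of −0.1 and half −0.5, so the average is −0.30. The added covariate is unrelated to outcome, treatment and instrument, but it is missing more often in the −0.5 group. Expected by hand for 20%/60% missing: the −0.5 group is 0.4/(0.8 + 0.4) = 1/3 of those retained, giving −(0.1 + 0.4/3) = −0.23. Simulated averages:

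| Missing, −0.1 / −0.5 group | Primary | Main list, restricted sample | Full list, restricted sample |
|---|---|---|---|
| 20% / 20% | −0.303 | −0.299 | −0.299 |
| 10% / 40% | −0.303 | −0.264 | −0.264 |
| 20% / 60% | −0.300 | −0.234 | −0.234 |
| 30% / 80% | −0.304 | −0.196 | −0.196 |

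Where missingness differs between the groups, the primary and secondary estimates differ by 0.04 to 0.11, and the middle column shows that all of this comes from the sample change. With equal missingness there is no material shift. This demonstrates the mechanism; it does not estimate its size in this study.

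**The case against.** - **The protocol never says a shift will be read as confounding.** Correct. A reader might infer that the authors commit to that reading, but Covariates and Missing data only announce an analysis with additional potential confounders. What remains is that comparison with the primary result is its evident use, and the stated design does not support that comparison.
- **It is not the plan's only safeguard.** Also correct. A reader might infer that nothing else guards against omitting these variables. In fact the IV design is the main protection: an omitted covariate biases an IV estimate only if it is related to the instrument. IV assumptions also promises to reassess each assumption in the full data. The documents do not show, however, that smoking, alcohol or lipids were among the covariates checked for balance.
- **The bridging fit may be in a fuller plan.** It may, and nothing excludes it. But the article itself fixes both covariate lists and both samples, and its general reference to other missing-data approaches does not supply the fit. Sensitivity analyses does plan to repeat objectives 1 and 2 in the HES-linked subset, which isolates a sample change there; the matching step is absent here.
- **The chance ranges rest on assumed inputs.** They do. The ±0.20 needs 80% recording and independent missingness of all seven variables, whereas lipid results are plausibly missing together. HES fills some missing ethnicity in the linked cohort. The feasibility counts also ignore losses from the primary complete-case restriction. A reader should not take two thirds of the 0.3 threshold as the expected discrepancy.

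**Conclusion.** The point holds as one of interpretation. A difference between the secondary and primary estimates, or the lack of one, cannot be attributed to the added confounders, because the sample changes through missingness the protocol itself expects to be substantial and non-random, and heterogeneous effects are averaged over whoever remains.

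A reader might infer that the primary estimate is therefore wrong. The documents do not support that: the primary analysis has its own sample and covariates, and this defect lies in a secondary analysis.

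The size of any shift is unknown. Under assumed 80% to 95% recording per variable, chance alone gives about ±0.05 to ±0.13 HbA1c points if the lipids are missing together and ±0.07 to ±0.20 if all seven are independent. Any selection effect would be additional and cannot be sized from the documents.

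**What to change.** Specify three fits, at least for the 12-month HbA1c outcome and the key long-term outcomes:

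- (a) main list in main-list complete cases, which is the primary analysis;
- (b) main list in full-list complete cases, which is new;
- (c) full list in full-list complete cases, which is the planned secondary analysis.

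Fit all three within the same bootstrap resamples, keeping the planned allowance for clustering within practices, so that the differences have proper intervals. Report (c) minus (b) as the effect of the added confounders among full-list complete cases only, and (b) minus (a) as the effect of the sample change. Tabulate the number and the baseline characteristics of people included in and excluded from the full-list sample.

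State that (c) minus (b) is not carried over to the whole primary sample without that caveat: with non-random missingness and heterogeneous effects, the added confounders may matter differently in the people excluded.

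No new data are needed. The cost is one further bootstrapped fit per outcome and contrast, which is not trivial for a model the protocol describes as demanding to compute; this is the reason to limit it to the main outcomes.
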